## Abstract

**Background:**

There are around 250 million adolescents in India. Adolescents are vulnerable to common mental disorders with depression and self-harm accounting for a major share of the burden of death and disability in this age group. Around 20% of children and adolescents are diagnosed with/ or live with a disabling mental illness. A national survey has found that suicide is the third leading cause of death among adolescents in India. The authors hypothesise that an intervention involving an anti-stigma campaign co-created by adolescents themselves, and a mobile technology-based electronic decision support system will help reduce stigma, depression, and suicide risk and improve mental health for high-risk adolescents living in urban slums in India.

**Methods:**

The intervention will be implemented as a cluster randomised control trial in 30 slum clusters in each of the cities of Vijayawada and New Delhi in India. Adolescents aged 10 to 19 years will be screened for depression and suicide ideation using the Patient Health Questionnaire (PHQ-9). Two evaluation cohorts will be derived—a high-risk cohort with an elevated PHQ-9 score ≥ 10 and/or a positive response (score ≥ 2) to the suicide risk question on the PHQ-9, and a non-high-risk cohort comprising an equal number of adolescents not at elevated risk based on these scores.

**Discussion:**

The key elements that ARTEMIS will focus on are increasing awareness among adolescents and the slum community on these mental health conditions as well as strengthening the skills of existing primary healthcare workers and promoting task sharing. The findings from this study will provide evidence to governments about strategies with potential for addressing the gaps in providing care for adolescents living in urban slums and experiencing depression, other significant emotional or medically unexplained complaints or increased suicide risk/self-harm and should have relevance not only for India but also for other low- and middle-income countries.

**Trial status:**

Protocol version – V7, 20 Dec 2021

Recruitment start date: tentatively after 15th July 2022

Recruitment end date: tentatively 14th July 2023 (1 year after the trial start date)

**Trial registration:**

The trial has been registered in the Clinical Trial Registry India, which is included in the WHO list of Registries (https://www.who.int/clinical-trials-registry-platform/network/primary-registries) Reference No. CTRI/2022/02/040307. Registered on 18 February 2022.

The tentative start date of participant recruitment for the trial will begin after 15th July 2022.

**Supplementary Information:**

The online version contains supplementary material available at 10.1186/s13063-022-06539-8.

## Background

There are around 250 million adolescents in India [1]. The 2016 National Mental Health Survey in India estimated that the prevalence of any mental illness among adults is about 15%, with nearly 150 million people in need of treatment [2]. The survey also found that adolescents are vulnerable to stress, depression, and increased risk of self-harm/suicide, which are leading causes of death and disability for this group in India. The prevalence of depression, stress, and substance use disorders accounts for most of the mental illnesses and is estimated to be around 10% [3]. Previous research has shown that India has relatively high suicide rates [4] that are particularly high among adolescents and young adults, and with wide variation in suicide rates across the country [5]. Data have shown that around 20% of children and adolescents experience a disabling mental illness [6].

### Treatment gaps for mental disorders in India among adolescents

The treatment gap (i.e. the difference between the number of people with a mental disorder and the number receiving appropriate treatment) for adults as well as adolescents with common mental disorders is large—estimated to be 75–95% in India, and further gaps in the quality of care are even more marked with around 4% of people with major depressive disorders receiving guideline-recommended care [7–9]. The reasons for these gaps are multifactorial, and demand-side barriers include limited awareness among many communities, low identification of individuals with mental illness, stigma, discrimination and negative community perceptions about mental health and help-seeking [10, 11]. Supply-side barriers include a lack of trained mental health professionals and lack of availability of specialist services [12, 13]. The availability of psychiatric health care professionals in high-income countries is approximately 75 to 120 times greater than in India [14] with the density of health care staff being much lower in rural areas.

### Need for community-based mental health services for adolescents

The Adolescents’ Resilience and Treatment nEeds for Mental health in Indian Slums (ARTEMIS) study seeks to address adolescent mental health through a community-based health service programme to deliver technology-enabled mental health services for disadvantaged adolescents in urban slums. Adolescents in slums face many stressors including poverty, academic stress, difficulties in relationships [15], unemployment, lack of education of parents [16], housing structure/living conditions [17], interpersonal violence (among males and females), low access to mental health care [18], and significant school dropout rates which increases their vulnerability. They also lack access to adequate support facilities, including health services. The ARTEMIS study also attempts to understand and quantify the stigma towards mental illnesses among adolescents in urban slum communities and to evaluate the impact of strategies to reduce this stigma through an extensive anti-stigma campaign.

In terms of interventions, a meta-analysis of community-based programmes for low-income urban youth indicated that for depression interventions a combined person-centred and environmental approach (such as involving families when appropriate) had the best effect [19]. However, existing studies are of varied quality and no age, gender, or geographical area-specific intervention data are available [20]. A review of stigma research found that adolescents prefer educational materials in either electronic or paper form as the main sources of information related to stigma, but the studies are limited and are non-existent from India or other low-and middle-income countries (LMICs) [21]. Two Indian studies have shown that basic mental health care delivery is possible by training lay health workers. However, such interventions involve recruiting additional personnel, which may affect scalability and generalizability for low-resource PHC settings [22, 23]. Other research has also shown that training primary health workers in delivering basic mental health care for stress, depression, and increased risk of self-harm/suicide is possible when suitably supported by evidence-based tools such as an anti-stigma campaign and technology-enabled mental health services delivery strategy [24].

To our knowledge, this trial is the first to focus on adolescents with mental illness in urban slum communities in India. The ARTEMIS study aligns with the Indian Government’s *Rashtriya Kishor Swasthya Karyakram (RKSK, National Adolescent Health Programme)* that focuses on adolescent health [25], and the National Mental Health Programme that emphasises the need for the delivery of innovative strategies by strengthening existing mental health care systems [26], as well as with WHO’s Comprehensive Mental Health Action Plan 2013-30 [14] at the international level. The study also aligns with the UN Sustainable Development Goal (SDG) of Good Health and Wellbeing by providing inclusive healthcare for adolescents in particularly disadvantaged communities and is directly related to the SDG Target 3.4.2 to reduce suicide rates [27]. To support these national and international programmes and goals, it is important that affordable, accessible, and effective treatments are available to tackle mental disorders, to strengthen individual resilience [28], to provide mental healthcare support and to create avenues to discuss mental health problems in a non-stigmatising manner.

### Mobile health (mHealth) strategies to support primary healthcare

Mobile health (mHealth) technologies are used to address access and treatment gaps for health conditions in primary healthcare settings, especially mHealth applications that seek to strengthen the capacity of the workforce using electronic decision support systems (EDSS). With the increased penetration of mobile devices, especially smart phones in India [29], the integration of EDSS into mobile devices (mobile phones, smartphones and tablets), can increase the reach into Indian communities. Studies conducted in high-income country settings have demonstrated the benefits of an EDSS in managing various health conditions, including mental health, especially for tools that use evidence-based algorithms to provide individualised advice at the point of care [30]. However, very few studies have been able to demonstrate improvements in clinical outcomes and most trials of such tools have resulted in improved processes of care only [31, 32]. In India, a systematic review of mHealth interventions found low-quality evidence on the efficacy, acceptability, and cost-effectiveness of such initiatives [33]. The ARTEMIS study will be contributing to filling in this gap by employing rigorous scientific evaluation to test the effectiveness of the mhealth component by using appropriate methods.

### Developing the intervention

In order to address these research gaps, the study’s aim is to develop and evaluate a complex intervention incorporating an anti-stigma campaign and a mobile technology-based EDSS to facilitate the delivery of mental health care for depression, other significant emotional or medically unexplained complaints, and increased risk of self-harm/suicide among adolescents living in urban slums. ARTEMIS will adapt the SMART Mental Health intervention [34] for adolescents (10–19 years) living in urban slums, in Vijayawada and New Delhi, and conduct a cluster randomised control trial (cRCT) to determine whether this strategy will increase remission rates for adolescents with depression, or increased risk of self-harm/suicide.

The two core components of the ARTEMIS intervention will be:An anti-stigma campaign to improve community behaviours toward adolescents with depression or increased risk of self-harm/suicide; andImplementation of a mobile device-based decision support system to improve the treatment of adolescents at high risk of depression or self-harm/suicide leading to higher remission rates from depression and reduced suicide risk.

### Anti-stigma campaign materials

Strategies used in the anti-stigma campaign straddle the three pillars of stigma namely, problems of knowledge (ignorance), problems of attitudes (prejudice) and problems of behaviour (discrimination) [35]. This includes the creation of educational materials to target inaccurate knowledge and stereotypes; interpersonal contact with members of a stigmatised community; and public protests against those who stigmatise other groups [21]. Reviews of anti-stigma campaigns have shown that interpersonal contact and to a lesser degree, educational materials, have been variably effective, with most evidence coming from high-income countries [36].

An important element of the ARTEMIS project is to establish an Adolescent Expert Advisory Group (AEAG) to guide researchers on all aspects of the project design, development and implementation. Three AEAG groups each will be formed in both of the sites; one a mixed group of younger adolescents (10 to 14 years) and two sex-segregated groups of older adolescents (15 to 19 years). The dynamics of engaging with adolescents and retaining them in a programme, especially in a LMIC, will be tested in consultation with the AEAG, as part of related doctoral research. Use of tools such as photo voice, social media, to discuss mental health issues will also be explored as part of the related doctoral research.

Formative research will be conducted to inform the development of information, education and communication (IEC) materials drawing on earlier research and adapting to the local context [37]. Preferences and suggested strategies will be sought from the community during the formative phase which includes, the adolescents themselves, and adults including parents and non-physician health workers (NPHWs), to implement an anti-stigma campaign for adolescents that is feasible and acceptable. These strategies will be designed by the AEAG and the intervention team to address the lack of awareness, misinformation about mental health among the slum communities, and will use education-based, interpersonal, and social contact approaches to increase knowledge, and reduce stigma, discrimination and social isolation related to depression and suicide/self-harm. The content will be developed in Telugu and Hindi, the most commonly spoken languages in the two study regions.

The content of the anti-stigma campaign will include the following:Printed IEC materials: brochures, flipbooks, and posters on signs and symptoms of depression, anxiety, substance use, and suicide risk/self-harm in adolescents; the need for seeking treatment and treatment/management options apart from medicines and psychotherapy; and stigma related to mental health prevalent in the community. Vignettes and infographics will be included in the brochures. Brochures and flipbooks will be used during door-to-door campaigns and community meetings during the intervention phase to raise mental health awareness and discuss problems related to stigma. NPHW such as Accredited Social Health Activists (ASHAs), Auxiliary Nurse Midwives (ANMs), and field staff will be involved in distributing these materials. The posters and pamphlets may also be shared with ward offices (a local authority area, typically used for electoral purposes), schools and urban primary health centres (UPHC) and displayed on their walls or notice boards.Videos: adolescents who experienced stress, depression, and thoughts of suicide/self-harm will talk about their experiences using video narratives of their lived experiences. Research has found such social contact –both direct and indirect (in the form of videos) with people with lived experiences to be beneficial in reducing stigma in the general public [38, 39]. These lived experience videos will be screened in the slums and discussed with adolescents, parents and other stakeholders as part of the anti-stigma campaign. Informed consent from the adolescents/their parents/guardians and assent will be sought before making these videos.Street theatre/plays: another method of indirect social contact that ARTEMIS will employ are street plays performed by adolescents themselves, supported by local street theatre groups highlighting mental health issues and help-seeking, as research shows that theatre are powerful mediums [40].Use of multimedia: two short animations on stigma concepts in line with that proposed by AEAG members will be produced and screened.

### mHealth-based EDSS

Separate EDSS modules will be developed for NPHW and UPHC doctors. The software will be developed on an Android platform, optimised for 7-inch tablets. The EDSS will include a screening tool based on the Patient Health Questionnaire (PHQ-9) [41, 42] which has been validated in India [43]. The PHQ-9 is available in the two vernacular languages spoken in Vijayawada and New Delhi and has been validated as an excellent tool for screening depression among adolescents [44]. The diagnostic and management guidelines that will be used by the UPHC doctor are based on WHO’s Mental Health Gap Action Programme- Intervention Guide (mhGAP-IG) [45] and focus on three conditions: depression, other significant emotional or medically unexplained complaints and self-harm/suicide. The mhGAP-IG is in English. The algorithm will be modified based on multiple iterations and feedback from the research team and a psychiatrist and has been validated in a previous mixed methods study [46]. The treatment algorithm provides guidelines about both pharmacological and psychological treatment including referral to a mental health specialist. A traffic-light dashboard called the priority listing app will also be included to support NPHWs to follow up high risk individuals and act on the treatment provided by the doctors.

The implementation of the mobile technology-based EDSS will include the following:Trained interviewers will administer the PHQ-9 to adolescents aged 10 to 19 years in the selected slum clusters to screen for depression and suicide/self-harm risk. They will use a tablet-based questionnaire to generate composite scores to identify ‘high-risk’ adolescents.NPHWs and doctors will be trained by the research team before the beginning of the intervention. Training of NPHWs and UHC doctors will be provided by in-person training and via the virtual conferencing platforms developed earlie r[24]. The NPHWs will then provide basic supportive advice such as engaging oneself in hobbies, strengthening social contact, and so on, and a referral to the UPHC doctor. High-risk adolescents will be electronically referred via the mHealth platform and provided with a paper referral card to take to the doctor.The UPHC doctor will then review adolescents at high risk as part of a health camp organised in the slum or examine the patient who may directly visit the UPHC. Data from adolescents at high risk will be uploaded, with their consent, to a secure health record using the Open Medical Record System (MRS) open source, electronic health record system.A decision support application based on WHO’s mhGAP-IG algorithm will be integrated in a tablet device and that will be used by UPHC doctors to diagnose and manage patients experiencing depression, other significant emotional or medically unexplained complaints and or having self-harm/suicide ideation. Doctors will use the depression, other significant emotional or medically unexplained complaints and self-harm/suicide modules of mhGAP-IG, especially related to adolescents. Adolescents at high risk of requiring medication can access these directly from the UPHC or purchase low-cost generic medication from a private pharmacy.For adolescents with complex needs, consultation with a specialist psychiatrist will be available as needed. The psychiatrist will also conduct case reviews via phone and/or video conferencing with the UPHC doctors to enhance their management skills. Alternatively, such adolescents can be referred by the UPHC doctor to a psychiatrist in the next tier of the public health system.NPHWs will conduct follow-up visits and assess treatment adherence using the traffic light system to guide them about the status of each high-risk adolescent catered to by a particular NPHW.

### Potential contributions to the field

This study will contribute to the literature on adolescents living in urban slums diagnosed with/ or live with mental disorders in low- and middle-income settings and will assess the potential impact of implementing an anti-stigma campaign about mental illness that has been co-created with adolescentsThis study will elucidate the barriers and facilitators for help-seeking by adolescents living in slums and diagnosed with/living with depression, other significant emotional or medically unexplained complaints or suicide/self-harmThis study will offer an understanding of the effect of using a combination of task sharing, an anti-stigma campaign and a technology-enabled mental health service delivery model to tackle depression, other significant emotional or medically unexplained complaints or increased suicide risk/self-harm among adolescents living in urban slums.The anti-stigma campaign will be one of the largest of such programmes for adolescents living in urban slums conducted in a LMIC.

## Research methods

### Aim

The study aims to test clinical effectiveness and cost-effectiveness of the implementation strategies to identify and reduce depression and suicide risk among adolescents living in urban slums. The study hypothesises that**:**A community-based anti-stigma campaign will lead to significant improvements in community behaviours toward adolescents with depression, other significant emotional or medically unexplained complaints and increased risk of self-harm/suicide; andA mobile device-based decision support system will improve the treatment of adolescents at high risk of depression, other significant emotional or medically unexplained complaints and increased risk of self-harm/suicide and lead to higher remission rates from depression and reduced suicide risk.

### Study design

A cluster randomised, control trial (cRCT) involving UPHCs in urban slum clusters in the cities of Vijayawada (in the state of Andhra Pradesh) and New Delhi will be conducted. The adolescent population will be screened to identify two cohorts: (1) adolescents at ‘high-risk’ of depression, suicide/self-harm; and (2) a random sample of adolescents not at high-risk. These will comprise the evaluation cohorts and they will be followed up for 12 months. Detailed process and economic evaluations will also be conducted (refer to Fig. 1 which outlines the study schema).

**Fig. 1 Fig1:**
[figure not shown]
Study schema

### Setting

The study will be conducted in two locations: slums clusters of Vijayawada and New Delhi. New Delhi is in the north of India, is the capital of the country and is the largest metropolitan city (population about 20 million) in India. Vijayawada is the second largest city in the south Indian state of Andhra Pradesh (population about 2 million). At each site, 30 slum clusters will be selected. For this study, a slum cluster is defined as slums within wards or geographical areas identified as slums/resettlement colonies. A ward is a local authority area, typically used for electoral purposes. In certain cities of India, such as Mumbai and New Delhi, a ward is an administrative unit of the city region; a city area is divided into zones, which in turn contain numerous wards. The slum clusters (constituting 1–5 slums) in Vijayawada, Andhra Pradesh and in New Delhi, under the Municipal Corporation of Delhi, will be selected from slums located within a radius of 60 km from the field office in both cities based on discussions with study collaborators and team members with prior experience working in these areas and will be selected to avoid contiguity. Each slum cluster will have a population of approximately 8000 and will be serviced by at least one UPHC. In Vijayawada, a few of the clusters selected lie in peri-urban areas but are informally considered as part Vijayawada both by local civil society organisations as well as by the Vijayawada municipality and are serviced by UPHCs and by the municipality.

### Eligible population

#### High-risk cohort

All consenting adolescents aged 10 to 19 years will be eligible for screening for depression, or suicide/self-harm risk. The screening will help to identify both high-risk and non-high-risk cohorts. High risk is defined as presence of at least one of the two conditions:High risk of depression based on PHQ-9 score ≥10.Positive response (score ≥2) to the suicide risk question on the PHQ-9.

Field investigators will continue screening until they have identified about 990 adolescents per location at high risk of depression or self-harm/suicide. This will form the ‘high-risk’ cohort. Because there will be some delay (up to 12 weeks) between screening and randomisation the high-risk adolescents will be rescreened to assess if they still meet the inclusion criteria prior to randomisation as literature suggests that around 25% of individuals initially identified at high risk will no longer meet the high-risk criteria at three months [47]. Only those adolescents who continue to remain at high risk during re-screening will form part of the high-risk cohort.

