### Statistical considerations

For high-risk adolescents, assuming a 50% remission rate in the control arm at 12 months based on published data [53], and 30 slum clusters per intervention location, at least 27 subjects per slum cluster are needed to detect a 15% absolute improvement in the intervention arm (65% intervention vs 50% control) at 12 months with 90% power. This assumes a 2-sided significance level of 0.05 and an intra-class correlation coefficient (ICC) of 0.1 based on pilot data [25]. To account for up to 20% of participants lost to follow-up, we will aim to enrol at least 33 participants per slum cluster for a total sample size of 1980 adolescents (60 clusters × 33 adolescents). Assuming a prevalence of 3% of adolescents with depression or increased risk of self-harm/suicide (48), we will therefore aim to screen about 1100 adolescents in each slum cluster. Further assuming that 5% of eligible adolescents will refuse to participate, we aim to screen 1160 adolescents in each slum cluster i.e. a total of 69,600 adolescents (60 slum clusters × 1160 adolescents).

Primary analyses will be conducted at the participant level using either random-effect generalised linear mixed models or generalised estimating equations adjusted for clustering. For the primary outcome, remission at 12 months differences will be assessed using a log-binomial (log link function) or logistic regression (log link function) including a random cluster effect. If using generalised estimating equations, the effect of clustering will be accounted for using a repeated cluster effect with a compound-symmetry variance-covariance structure. The intervention effect will be estimated as odds ratio and corresponding 95% confidence interval.

Sub-group analyses will be conducted according to UPHC-level characteristics (size, location and health service characteristics) and patient-level characteristics (demographic factors and clinical factors e.g. depression severity at baseline). The primary outcome will be assessed at 12 months (and reported as secondary outcomes at 3 and 6 months).

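### The identification and screening targets leave out the plan's own expected 25% loss at re-screening, so the stated 1,980 and 90% power do not follow from its inputs; the cohort shortfall is large, the power loss modest

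*Protocol article*

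**What the plan says.** The High-risk cohort section of the Protocol article gives the field rule: "Field investigators will continue screening until they have identified about 990 adolescents per location at high risk of depression or self-harm/suicide". The article says that this group will be the high-risk cohort. It then describes a gap of up to 12 weeks before randomisation and a re-screening, because "around 25% of individuals initially identified at high risk will no longer meet the high-risk criteria at three months". The section closes: "Only those adolescents who continue to remain at high risk during re-screening will form part of the high-risk cohort".

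Statistical considerations states that "at least 27 subjects per slum cluster are needed" for 65% against 50% remission "at 12 months with 90% power", with a two-sided 5% level and an ICC of 0.1. To allow for up to 20% loss to follow-up, "we will aim to enrol at least 33 participants per slum cluster for a total sample size of 1980 adolescents". The screening number is then built up from 3% prevalence (1,100 per cluster) and 5% refusal (1,160 per cluster, 69,600 over 60 clusters). Re-screening is not mentioned there.

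**The concern.** A count of 990 taken before an expected 25% loss cannot still be 990 after it. The number at which first screening stops equals the number that must be enrolled, and the screening workload is calculated from the same 33 per cluster. The plan states the attrition in one section and does not carry it into either target.

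At stake are the size of the high-risk cohort, on which the remission outcome is analysed, the stated power, and the field workload. The Abstract sets the low-risk cohort equal in number to the high-risk cohort, so the combined cohort for the anti-stigma outcome would shrink in step, from 2 × 1,980 = 3,960 to 2 × 1,485 = 2,970.

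**Working it through.** **Inputs, all from the Protocol article.** Remission 50% against 65%; two-sided alpha 0.05; 90% power; ICC 0.1; 33 enrolled per cluster; 20% loss to follow-up; 3% prevalence; 5% refusal (Statistical considerations). 60 clusters (Setting) allocated 1:1 (Randomisation), so 30 per arm. About 25% loss at re-screening (High-risk cohort).

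**1. The plan's sample size reproduces.**
- Unclustered n per arm = (1.96 + 1.2816)² × (0.25 + 0.2275) / 0.15² = 223.
- With design effect 1 + (m − 1) × 0.1 and 30 clusters per arm, solve 30m = 223 × (1 + 0.1(m − 1)): m = 26.1, so 27 after rounding up.
- At m = 27: design effect 3.6, effective n = 810 / 3.6 = 225 per arm, power 90.3%. A pooled variance gives 89.9%.
- Enrolment: 27 × 1.2 = 32.4, rounded up to 33. This leaves 33 × 0.8 = 26.4 analysable, with power 90.1% (pooled 89.7%). This is the fair baseline for what follows.

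**2. The plan's screening numbers reproduce without any re-screening term.**
- 33 / 0.03 = 1,100; 1,100 / 0.95 = 1,158, stated as 1,160; × 60 = 69,600.
- In reverse: 1,160 × 0.95 × 0.03 = 33.1 first-screen positives per cluster. That is the enrolment target, reached before re-screening.
- 30 × 33 = 990 per location, the stated stop.

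**3. Apply the plan's 25%.**
- Cohort: 33 × 0.75 = 24.75 per cluster; 990 × 0.75 = about 742 per location; 1,980 × 0.75 = 1,485 in total, which is 495 short.
- Analysable: 24.75 × 0.8 = 19.8 per cluster.
- Design effect 1 + 18.8 × 0.1 = 2.88; effective n = 30 × 19.8 / 2.88 = 594 / 2.88 = 206 per arm.
- z = 0.15 / √(0.4775 / 206.25) = 3.117; power = Φ(3.117 − 1.960) = 87.6% (pooled 87.2%).
- The fall from the baseline is about 2.5 points on either variance.

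**4. Range for the re-screening loss.** Values other than 25% are assumptions.

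| Loss | Enrolled per cluster | Analysable per cluster | Power (unpooled / pooled) |
|---|---|---|---|
| 0% | 33 | 26.4 | 90.1% / 89.7% |
| 10% | 29.7 | 23.8 | 89.3% / 88.9% |
| 15% | 28.05 | 22.4 | 88.8% / 88.4% |
| 25% (plan) | 24.75 | 19.8 | 87.6% / 87.2% |
| 35% | 21.45 | 17.2 | 86.1% / 85.6% |

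**5. Numbers needed for 33 per cluster after re-screening.** 33 / 0.75 = 44 first-screen positives per cluster, or 1,320 per location. Screening: 44 / 0.03 / 0.95 = 1,544 per cluster, × 60 = about 92,600.

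**The case against.** The best defence is that 33 is an enrolment floor, that enrolment into the cohort follows re-screening, and that the 990 is said to be the cohort. On that reading screening simply continues until 990 are confirmed, and no one is missing. This stands as a possible reading, and it removes the cohort shortfall. It does not rescue 1,160 and 69,600, which contain no re-screening term and would then be about a quarter below what is needed (1,160 against 1,544).

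The second defence is that 25% belongs to a full three months, while the delay is up to 12 weeks, so the average loss could be smaller. That is fair, and it is why a range is given. No loss in that range makes the targets agree with one another.

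The third defence is that the effect on power is small. This stands. With an ICC of 0.1 and 60 clusters fixed, the number per cluster adds little, and all 60 clusters are still randomised. Comparing 19.8 with 27 also slightly overstates the effect of re-screening, because the plan's own 33 × 0.8 gives 26.4.

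A reader might go further and infer that the trial is seriously underpowered, for instance because the stop is counted per location and cluster sizes could then vary widely. The document does not support this. Statistical considerations sets both enrolment and screening per cluster, Setting plans clusters of similar population, and no figure for variation in cluster size is given. Any such variation would lower power with or without re-screening, so it is a separate matter.

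**Conclusion.** The point holds as an inconsistency between the plan's targets and its own stated attrition. On the plain order of the text, which places identification before re-screening, the expected high-risk cohort is about 1,485 rather than 1,980, a quarter short. Power is then about 87–88% rather than about 90%. If 990 is a post-re-screening count, the error is confined to the screening numbers.

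The power figures assume equal cluster sizes, an ICC of 0.1, 30 clusters per arm, 20% loss to follow-up, and the full 25% re-screening loss. That 25% comes from a cited source not available here. The shortfall does not threaten the design, the analysis or the interpretation of the trial. It should be fixed because the published sample size, screening workload and power do not follow from the stated inputs, but it is not a critical flaw.

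**What to change.** State in the High-risk cohort section and in Statistical considerations whether 990 per location and 33 per cluster are counted before or after re-screening. Then do one of two things:

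- **Count after re-screening.** Restate the screening numbers that follow: 44 first-screen positives per cluster (1,320 per location), about 1,545 screened per cluster and about 92,600 in total. This is about 23,000 more adolescents than the 69,600 planned, for about 2.5 points of power, so it is not cheap. The article gives a cluster population of about 8,000 but not the number of adolescents in it, so feasibility would need checking first.
- **Keep the present screening.** Restate the expected cohort (about 1,485, or 24.75 per cluster) and the power (about 87–88%, with the range for a smaller loss). This costs only wording and is proportionate to the size of the problem.
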